
## Methods/Design

### Trial design

We are conducting a multicenter, parallel-group, randomized, controlled trial comparing NET to a waiting list condition and TAU at several treatment units located in Finland. Five sets of assessments will be carried out: baseline, T0 (3 months before the start of treatment); pre-test, T1 (when treatment begins); during treatment, T2 (approximately halfway through the treatment); post-test, T3; and follow-up, T4 (three months after treatment). A three-month follow-up period is considered long enough to assess medium-term maintenance of treatment gains, but still short enough to be practically implementable in this context, where drop-outs due to, e.g., asylum seekers being denied asylum and leaving the country, are possible. A three-month follow-up period also means that the T0, T1, T3 and T4 measurements are conducted at equal intervals of three months. Table 1 presents the measurements taken at each point of assessment.

**Table 1 Tab1:** Points of assessment and measures used

T0 Baseline	T1 Pre-test	T2 Midpoint	T3 Post-test	T4 Follow-up
Approx. three months before start of treatment	At start of treatment	Approx. halfway through treatment	Immediately after treatment	Three months after treatment
– CRIES	– CRIES	– CRIES	– CRIES	– CRIES
– DSRS	– DSRS	– C-PTCI	– DSRS	– DSRS
– SDQ	– SDQ	– TMQQ	– SDQ	– SDQ
– C-PTCI	– C-PTCI	– SUDS (each session)	– C-PTCI	– C-PTCI
– CYRM	– CYRM		– TMQQ	– TMQQ
– TMQQ	– TMQQ		– CYRM	– CYRM
– PDEQ			– CSRS	– CSRS
For subsample:				For subsample:
– WMTB-C				– WMTB-C
– RPM				– RPM
– TMT				– TMT

*C-PTCI*, Children’s Post-Traumatic Cognitions Inventory; *CRIES*, Children’s Revised Impact of Event Scale; *CSRS*, Child Session Rating Scale; *CYRM*, Child and Youth Resilience Measure; *DSRS*, Depression Self-Rating Scale for Children; *PDEQ*, Peritraumatic Dissociative Experiences Questionnaire; *RPM*, Raven’s Progressive Matrices; *SDQ*, Strengths and Difficulties Questionnaire; *SUDS*, Subjective Units of Distress Scale; *TMT*, Trail Making Test; *TMQQ*, Trauma Memory Quality Questionnaire; *WMTB-C*, Working Memory Test Battery for Children

There are two control conditions. First, the time each child spends waiting for treatment to begin, typically three months, will be considered a waiting list control condition. Second, each participant will be randomized into one of two groups. One group will receive NET, acting as the study group, and the other group, receiving TAU, will act as a positive-control group. The trial is parallel-group in nature, with a randomized block design with varying block sizes and an allocation ratio of 1:1.

### Study locations

Most of the interventions will be carried out at three co-operating outpatient clinics and two inpatient wards, all places where traumatized children of immigrant background would in any case receive treatment. These clinics and wards are 1) the Family Counselling Centre of the City of Tampere, 2) the Psychiatric Clinic for Traumatized Children at Tampere University Hospital, 3) the Adolescent Psychiatry Clinic at Tampere University Hospital, 4) the Psychiatric Treatment and Research Unit for Adolescent Intensive Care (EVA) at Tampere University Hospital, and 5) the Centre for Torture Survivors (Helsinki Deaconess Institute). In addition, some participants may be recruited by and receive treatment from co-operating individual therapists operating privately.

### Planned interventions

Figure 1 shows the flow diagram of experimental vs. control situations in the study design.

**Fig. 1 Fig1:**
[figure not shown]
Adapted CONSORT flow diagram. Adapted CONSORT flow diagram, illustrating the study design, the flow of participants in the study and the planned assessments

#### NET intervention

For the intervention group receiving Narrative Exposure Therapy treatment, the intervention will last for approximately three months and include 10–12 weekly sessions of 60–90 min. The course of the intervention will follow the NET manual [14].

The NET intervention begins with a clinical assessment (partly already collected during the T0 measurement), collecting demographic data, and assessing current complaints. This pre-treatment diagnostic session is followed by a session of psychoeducation, which includes explaining the child’s current condition to him/her in a way that helps her/him understand the diagnosis and the purpose of the treatment. After diagnosis and psychoeducation, the narrative exposure portion of the intervention begins. During the first narrative session, the child and the therapist construct a lifeline for the child, with a rope/string representing his/her life from birth up to the present. Next, flowers and stones are placed on the lifeline at chronologically corresponding locations to represent happy moments in life and difficult, fearful or painful moments, respectively. Other symbolic elements may also be used for other significant life events.

The following sessions are generally each devoted to processing a single traumatic event through narrative exposure. Thus, the number of narrative sessions depends on the number of events identified on the lifeline, but should generally be limited to 6–9 weekly sessions. The chronology of the narration during the intervention follows the lifeline, addressing all traumatic incidents throughout the course of the child’s biography, accompanied by other turning points in her/his life. In each session, the therapist writes down the child’s narration. In the subsequent session, the narrative from the previous session is read aloud to the child, and the child is asked to correct it or add any details that may have been missed. The procedure is repeated in subsequent sessions until a final version of the child’s biography is created. In the last session, the biography as a whole is read aloud to the child. The child and the therapist sign the written narration. One copy is handed to the child. Another is kept for research purposes, provided that permission for this is obtained.

All clinicians providing treatment will receive a three-day training on NET by instructors experienced in the method. Each participating unit will be provided with NET manuals. For the NET intervention group, clinicians are instructed to adhere as strictly as possible to the intervention as laid out in the NET manual. Semi-annual supervisory meetings will be organized with the clinicians and the research team to discuss the use of the treatment method and any issues in implementing it that may have appeared. The developers of the method are also available for supervisory purposes via Skype.

#### Control intervention

For the TAU control group, participants will receive the usual care for posttraumatic stress symptoms currently offered by each unit. This treatment may last for more than the three months the NET intervention will take, but T3 measurements will in any case be collected three months after treatment has started. No specific instructions will be given to clinicians as to what TAU should entail, apart from not including elements specific to NET. Thus, in keeping with the pragmatic goal of studying the effectiveness of NET as compared to current usual care, the TAU provided by clinicians at cooperating units will vary and include whatever methods they have used until now. These methods are likely to include the use of (TF-)CBT, Eye Movement Desensitization and Reprocessing and forms of family therapy. Information about the kind of treatment offered to each participant in the control group will be collected.

### Participants

The participants of the study are up to 80 children (between 9 and 17 years of age) living in Finland who will attend Narrative Exposure Therapy or treatment as usual for posttraumatic stress symptoms due to exposure to armed conflict. As no war or major organized violence has taken place in Finland for decades, these participants will be immigrants, refugees or asylum seekers. The sample will be collected among all eligible children who are clients of (a) The Family Counselling Center of the City of Tampere, (b) The Psychiatric Clinic for Traumatized Children at Tampere University Hospital, c) The Adolescent Psychiatry Clinic at Tampere University Hospital, d) the Psychiatric Treatment and Research Unit for Adolescent Intensive Care at Tampere University Hospital, e) The Centre for Torture Survivors of the Helsinki Deaconess Institute or f) co-operating individual private practitioners trained in NET.

#### Inclusion and exclusion criteria

Inclusion and exclusion criteria applied to clinical research on PTSD vary widely, with no established standards [48]. In keeping with the aim of carrying out a pragmatic trial in usual care settings, this trial aims for a great variety of participants with few exclusion criteria. Thus, only acute psychosis or marked intellectual disability will be considered definite criteria for exclusion, while other comorbid conditions such as depression, generalized anxiety disorder or obsessive-compulsive disorder will not. Generally, any child between 9–17 years old who a) has spent some part of her/his life living in a country where organized violence was taking place, or at a refugee camp, and b) suffers from significant stress symptoms thought be trauma-related, may be included in the study. All children will be clinically assessed at the start of treatment, but a formal diagnosis of PTSD is not required.

### Measures

#### Primary outcomes

*Posttraumatic stress symptoms* will be measured at T0, T1, T2, T3, and T4, employing the children’s version of the Revised Impact of Event Scale (CRIES) [49]. CRIES consists of 13 items covering the re-experiencing, avoidance and hyperarousal symptom dimensions. Children estimate the occurrence of each symptom on a 4-point scale. CRIES-R has been found to have good reliability among war-affected children [50].

*Depressive symptoms* will be measured at T0, T1, T3, and T4 employing the Depression Self-Rating Scale for Children (DSRS) [51]. The measure includes 18 items that assess the cognitive, affective, and behavioral dimensions of depression. At each item, children estimate on a 3-point scale whether they have experienced the symptom over the preceding two weeks.

*Psychological distress* will be measured at T0, T1, T3, and T4 employing the Strengths and Difficulties Questionnaire (SDQ) [52]. One form is provided for self-assessment by the child and another for a parent or guardian, if available. The measure covers emotional and behavioral problems and hyperactivity. Each dimension consists of 5 items evaluated on a 3-point scale as to how well the description fits the situation of the child.

*Resilience* will be measured at T0, T1, T3, and T4 using an adapted, focus-group-based version of the Child and Youth Resilience Measure (CYRM) (28-item version originally developed by Ungar and Liebenberg [53], and validated in [54]). CYRM is a questionnaire exploring the individual, relational, communal and cultural resources that may bolster the resilience of 9–23-year-old youth. The participant reports on a 5-point scale as to what extent he/she feels he/she has certain resources.

*Cognitive performance (of a subset of participants)* will be addressed by measuring a) attention and working memory, b) non-verbal, general cognitive performance and c) executive functioning. Attention and working memory will be measured at T0 and T4 employing performance-based sub-tests for verbal and spatial working memory from the Working Memory Test Battery for Children (WMTB-C) [55]. Non-verbal, general cognitive performance will be assessed at T0 and T4 employing age-appropriate versions of Raven’s Progressive Matrices (RPM) [56]. Executive functioning will be measured at T0 and T4 employing the Trail Making Test (TMT) [57].

#### Secondary outcomes and mediators

*Quality of traumatic memory* will be assessed at T0, T1, T2, T3, and T4 employing the Trauma Memory Quality Questionnaire (TMQQ) [58]. The measure contains 11 items related to the visual quality, non-visual sensory qualities (e.g., auditory, olfactory and proprioceptive sensations), and temporal context of the traumatic memory, as well as to the extent to which the memory is in a verbally accessible format. Participants evaluate each item on a 4-point scale as to how much they agree with the statements.

*Trauma-related cognitions* are measured at T0, T1, T2, T3, and T4 using the Children’s Post Traumatic Cognitions Inventory (C-PTCI) [59]. The measure includes 25 statements on the kinds of thoughts and feelings the child has had after the traumatic event, e.g., “I feel like I am a different person since the frightening event.” Children evaluate on a 3-point scale how well the descriptions fit them.

*General functioning of autobiographical memory* will be explored, in the intervention group only, by tracking the number of life events initially identified at the start of the intervention, as well as the recovery of new events and possible temporal reorganization of life events during therapy. In addition, the written life narratives that result from NET treatment will be coded for (1) emotional tone (positive vs. negative), (2) thematic lines (agency and communion), and (3) narrative complexity [60], as well as for sequences of redemption and contamination [61].

#### Additional measures: moderators and measures related to therapeutic interaction

*Peritraumatic dissociation* will be assessed at T0 using the Peritraumatic Dissociative Experiences Questionnaire (PDEQ) [62]. The measure assesses the level of dissociation at the time of the traumatic event and immediately after it. 10 items are evaluated on a scale from 1 (not true at all) to 5 (extremely true).

*Cognitive performance* at T0, measured as described above, will also be treated as a possible moderator.

*Distress during the therapeutic intervention* is measured several times during each treatment session using the Subjective Units of Distress Scale (SUDS) [63]. The level of distress is measured in order to guarantee the safety of the intervention as well as to obtain data on the intrusiveness of narratives. SUDS consists of a thermometer-like scale from 0 to 10 that measures the subjective intensity of disturbance or distress currently experienced by the participant. When prompted, the child points to or otherwise indicates where he/she is at on the scale at the moment. SUDS is commonly used as a benchmark for a professional or observer to evaluate the progress of treatment.

*Intervention effectiveness and effective treatment components from the client’s point of view* are assessed with the Child Session Rating Scale (CSRS) [64], administered at T3. In the CSRS, the child evaluates five dimensions of interaction during the intervention by marking a point on a line segment.

### Procedure

A sequential procedure will be applied to data collection. Whenever a child is identified as a potential participant by a clinician at one of the co-operating units, information concerning the intervention and the related research is provided both to the participant him/herself and to his/her parents. If they are willing to participate in the research, informed consent will be requested from the child and his/her parents.

Waiting list control baseline data (T0) will be collected during this first meeting with the clinician. The children will then be randomly assigned to EITHER the ‘treatment as usual’ group (n = 40) OR the ‘NET intervention’ group (n = 40). Because of the treatment queues currently present at most of the treatment units, all participants will first be placed under waiting-list conditions for approximately three months (waiting list control condition, n = 80). In the unlikely case that there is no treatment queue at the moment, the participant will begin NET or TAU immediately and will not contribute waiting list control data.

At the start of the intervention or TAU, pre-test (T1) data will be collected from all participants. The T1 data will serve as an end measurement for the waiting list control condition and as the pre-test measurement for the NET intervention and the TAU control condition.

Data (T2) will also be collected once during the treatment for both the NET and the TAU groups. This will allow for proper analysis of mediating mechanisms. In the NET group, this assessment will take place at the time when the worst traumatic memories have been narrated.

Post-test data (T3) will be collected from participants in both groups, immediately after the intervention for the NET group, and after three months of treatment for the TAU group, and follow-up data (T4) will be collected during a joint family meeting, three months later.

In most cases, the clinician working as the therapist will also act as the assessor and collect data from the patients he/she is treating. In some cases, members of the research team may carry out some assessments, particularly for follow-up. Interpreters are used whenever needed during assessments, and will be present during all assessment and treatment sessions for children who are not fluent in Finnish.

The procedure will be continued until the sample size reaches the goal of n = 80, with data collection estimated to finish during 2017.

Due to restrictions on the use of the tests used for measurements of cognitive performance, these additional assessments will be carried out by a member of the research team (SK), a licensed clinical psychologist, and studied in a smaller subsample. For n = 20 participating children about to start treatment during 2015, willingness and informed consent to participate in these additional tests will be requested, and the measurements will then be carried out at T0 and T4 for this subsample.

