**Methods/Design:**

We are conducting a multicentre, pragmatic RCT in a usual care setting. Up to 80 9–17-year-old immigrant children who have experienced war and suffer from PTSD symptoms will be randomized into intervention (NET) and control (treatment as usual, TAU) groups of equal sizes. The effectiveness of NET treatment will be compared to both a waiting list and the parallel TAU positive control group, on the primary outcomes of PTSD and depressive symptoms, psychological distress, resilience, and level of cognitive performance. The effects of the intervention on traumatic memories and posttraumatic cognitions will be studied as potential mechanisms of change mediating overall treatment effectiveness. The possible moderating effects of peritraumatic dissociation, level of cognitive performance, and gender on treatment effectiveness will also be considered. We hypothesize that NET will be more effective than a waitlist condition or TAU in reducing PTSD and other symptoms and improving resilience, and that these effects will be mediated by changes in traumatic memories and posttraumatic cognitions.

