### Research questions and hypotheses

This study will address the effectiveness of NET in treating trauma-related symptoms and improving resilience and cognitive performance. The mediating roles of trauma-related cognitive appraisals and memory functions on this effectiveness will also be studied, as well as several moderators potentially affecting recovery. Accordingly, the research questions are as follows.Does NET reduce a) posttraumatic stress disorder symptoms, b) depressive symptoms and/or c) psychological distress symptoms in children traumatized by war more effectively than a waiting list condition or treatment as usual? Does NET increase resilience or improve cognitive performance?The hypothesis is that NET is more effective in reducing PTSD, depressive and psychological distress symptoms as well as in increasing resilience and improving cognitive performance than TAU or a waiting list condition, to a statistically and clinically significant degree.What changes in the participants’ trauma-related memory functions and cognitions can be observed as a result of NET treatment, as compared to a waiting list condition and treatment as usual?The hypotheses are that statistically significant differences between the NET group and the control groups will be found in the participants’ trauma-related memory functions and cognitions at the end of treatment. It is hypothesized that at the end of treatment, NET participants will show lower levels of overgeneralization and fragmentation in their autobiographical memories, as compared to baseline, as well as more spatial and temporal contextualization and coherence. The trauma memories of children after NET are expected to be less biased and intrusive as compared to controls, and include more verbal and fewer sensory elements. Finally, it is hypothesized that participants in the NET group exhibit greater reductions in dysfunctional trauma-related cognitive appraisals, as compared to the waiting list and TAU groups.To what extent do these changes in trauma-related memory functions and cognitions mediate the effectiveness of NET in reducing PTSD symptoms, depressive symptoms and psychological distress symptoms, increasing resilience and improving cognitive performance?The hypothesis is that beneficial changes in autobiographical memory, trauma-related memories and trauma-related cognitive appraisals partly explain the reduction in at least PTSD and depressive symptoms among children who participate in NET, and may contribute to increased resilience and improved cognitive performance.To what extent does level of peritraumatic dissociation, level of cognitive performance or gender moderate the effectiveness of NET in reducing trauma-related symptoms?The hypothesis is that participants with very high levels of peritraumatic dissociation benefit less from the intervention in terms of symptom reduction. Girls and children with higher levels of cognitive performance are hypothesized to benefit more from the intervention.

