### Statistical analyses

#### Basic analyses

The sample and its characteristics will be analysed employing descriptive statistical methods. Means, standard deviations and other basic statistics for all relevant variables will be calculated for descriptive purposes. Between-group comparisons at baseline will be performed to test randomization and assess differences between treatment and control groups, as well as between participants at different study locations. The internal reliabilities of the instruments used will be analysed employing Cronbach’s α. For all statistical tests, significance levels will be set at α = 0.05, with the Holm-Bonferroni method used to control family-wise error rates, where appropriate. Multiple imputation will be employed in the case of dropouts or other missing data. Intention-to-treat analyses will be carried out, so that all participants who are randomized into either group will be included in final analyses.

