#### Effect evaluation

The main effect of NET as compared to TAU and the waiting list control condition on the primary outcomes of PTSD symptom severity, depressive symptoms, psychological distress, resilience and cognitive performance will be analysed employing analyses of covariance. Potential confounding factors (age, gender, treating unit) will be included as covariates. The main effects of NET as compared to TAU and the waiting list condition on the secondary outcomes of trauma memory quality and trauma-related cognitions will be similarly analysed employing analyses of covariance. For all analyses of covariance, effect sizes will be reported as partial η^2^, with 95 % confidence intervals included.

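### Cognitive performance is a primary outcome to be compared with the waiting list, but it is tested only at T0 and T4 in 20 children, so that contrast cannot be estimated and the TAU contrast is severely underpowered

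*Protocol article*

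**What the plan says.** The abstract compares NET with both controls "on the primary outcomes of PTSD and depressive symptoms, psychological distress, resilience, and level of cognitive performance". The Primary outcomes section also lists cognitive performance, noting that it is measured in a subset. The hypothesis under Research questions and hypotheses is that NET does better at "improving cognitive performance than TAU or a waiting list condition, to a statistically and clinically significant degree". Effect evaluation repeats the promise: "The main effect of NET as compared to TAU and the waiting list control condition on the primary outcomes of PTSD symptom severity", and the list continues to "resilience and cognitive performance will be analysed employing analyses of covariance".

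Trial design defines the waiting list as the time each child spends waiting for treatment, typically three months. Procedure makes T1 the end measurement of that condition.

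Table 1 and Primary outcomes place the three cognitive tests (WMTB-C, RPM, TMT) at T0 and T4 only. Procedure agrees: "For n = 20 participating children about to start treatment during 2015", consent is sought for the extra tests, and "the measurements will then be carried out at T0 and T4 for this subsample".

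The T0 scores have a second use. Under Additional measures, cognitive performance "at T0, measured as described above, will also be treated as a possible moderator", and the hypotheses predict that children with higher performance benefit more.

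**The concern.** A primary outcome carries a stated hypothesis with two comparisons. One needs a measurement that the schedule does not contain. The other rests on a quarter of the planned sample (20 of 80), although the sample size section justifies its figure for covariance analyses on the primary outcomes generally.

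Two things are at stake. The report will either leave a promised primary comparison unanswered or fill it with something else, such as the whole T0–T4 change, which mixes waiting, treatment and follow-up. And a non-significant NET versus TAU result on a primary outcome could be read as evidence that NET does not help cognition, when the data could not have shown a moderate effect.

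**Working it through.** **Step 1. Can the waiting-list change be formed?**

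- Waiting-list interval: T0 to T1 (Trial design, Procedure).
- Cognitive tests: T0 and T4 (Table 1, Primary outcomes, Procedure).
- A waiting-list change needs T1 minus T0. There is no T1 value, so it does not exist for any child. There is no T3 value either, so the one available change, T4 minus T0, spans about nine months: three waiting, three in treatment, three of follow-up.
- Children who start treatment at once do not help. Procedure says they supply no waiting-list data.

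This step needs no assumption, and no later analysis document can supply the missing measurement.

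**Step 2. Reproduce the protocol's 52.**

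Inputs from Sample size calculation: α = 0.05, f ≈ 0.40 (from d = 0.85), power 0.80. For two groups, power is the upper tail of a noncentral F with 1 and N − 2 − (covariates) degrees of freedom and noncentrality λ = f²N.

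At N = 52 and f = 0.40, λ = 0.16 × 52 = 8.32 and power is 0.807. The smallest N reaching 0.80 is 52, so the figure reproduces. (Without rounding, f = 0.85/2 = 0.425 gives N = 46.)

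**Step 3. Apply the same formula to the subsample.**

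N = 20, taken as 10 per arm from the 1:1 allocation, with no dropout. This is 20/52 = 38% of the protocol's requirement. With f = d/2 and no adjustment for T0:

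- d = 0.85: λ = 0.425² × 20 = 3.61, power 0.436.
- d = 0.5: λ = 0.25² × 20 = 1.25, power 0.185.
- d = 0.3: power 0.097.
- Effect detectable with 80% power: d = 1.325.
- Uneven split of 6 and 14: power at d = 0.85 falls to 0.38.

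All 80 children would give 0.96 at d = 0.85 and 0.60 at d = 0.5.

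**Step 4. Allow for adjustment by the T0 score.**

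The protocol gives no T0–T4 correlation r, so a range is assumed. With one covariate, f = (d/2)/√(1 − r²):

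| r (assumed) | Power, d = 0.85 | Power, d = 0.5 | Detectable d |
|---|---|---|---|
| 0 | 0.434 | 0.184 | 1.33 |
| 0.5 | 0.544 | 0.230 | 1.15 |
| 0.7 | 0.708 | 0.315 | 0.95 |
| 0.8 | 0.847 | 0.420 | 0.80 |

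For example, at r = 0.7 and d = 0.85, λ = 3.6125/0.51 = 7.08. Three further covariate degrees of freedom lower each power figure by about 0.01 or less.

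**The case against.** The best defence is that the protocol already treats cognition modestly. The Current trial section speaks of exploring it in a subsample, the Discussion uses similar language, and Procedure gives a practical reason for the small number: the tests may be given only by a qualified member of the team. The trial was sized on PTSD severity, and that comparison is untouched. All of this stands. It makes the repair easy, but it does not remove the primary label, the hypothesis or the promised waiting-list contrast.

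The defence is also right that the NET versus TAU contrast should not be called nearly powerless. A T0-adjusted analysis with a strong correlation would have fair or even adequate power at d = 0.85. That effect, however, is the protocol's figure for PTSD severity against a waiting list. None is given for cognition or for NET versus TAU, and the protocol expects TAU to have some effect.

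A reader might infer several stronger points that the document does not support:

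- **Consent to testing depends on the allocated arm.** The wording "For n = 20 participating children about to start treatment during 2015" invites this. But Procedure puts T0 data collection before randomization, and the tests are at T0. The wording is ambiguous, because T0 lies about three months before treatment; it does not show that consent follows allocation.
- **The 60 untested children would be imputed.** The rule reads "Intention-to-treat analyses will be carried out, so that all participants who are randomized into either group will be included in final analyses", and multiple imputation covers missing data. But Primary outcomes limits this measure to a subset, and nothing says that children never selected for testing would receive imputed scores.
- **Cognition tightens the Holm thresholds for the other outcomes.** Holm-Bonferroni is to be used where appropriate, and no family is defined.
- **A specific power figure for the moderator.** Any figure based on a median split would describe an analysis the protocol does not propose; it plans conditional process analysis. A moderator test in 20 children is weak by any method, and that is as far as the text goes.

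**Conclusion.** The point holds in two parts of different strength.

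The waiting-list contrast for cognitive performance cannot be estimated. This follows from the protocol's own definitions and schedule and rests on no assumption.

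The NET versus TAU contrast can be estimated but is severely underpowered for a primary outcome: 20 children against a stated requirement of 52. Power is 0.44 unadjusted at d = 0.85, and 0.54 to 0.85 with T0 adjustment at assumed correlations of 0.5 to 0.8. At d = 0.5 it is about 0.19 unadjusted and 0.23 to 0.42 adjusted. Only the combination of a large effect and a correlation near 0.8 reaches the planned 0.80. These figures assume 10 per arm, no dropout and a two-sided test at 0.05; the correlations and the effect sizes for cognition are assumptions.

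The cognitive-performance moderator analysis rests on the same 20 children and cannot carry a confirmatory hypothesis. The defect is confined to the cognitive claims and leaves the PTSD comparison intact.

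**What to change.** 1. Move cognitive performance from the primary to the exploratory outcomes in the abstract, Primary outcomes and Effect evaluation, in line with the exploratory language in the Current trial section.
2. Delete the waiting-list comparison for this outcome from the hypothesis and from Effect evaluation.
3. Specify the analysis as T4 adjusted for T0, NET versus TAU, in the tested children only, reported with confidence intervals.
4. Label the analysis of cognitive performance as a moderator exploratory.
5. Clarify in Procedure that consent to testing and the T0 tests come before the envelope is opened, and reword the description of the subsample so that it fits testing at T0.

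The cost is wording; no new data are needed. The downside is that the cognitive claims become exploratory. If cognition is to remain primary, the alternative is a cognitive assessment at T1 and a subsample size justified for this outcome. That means more testing under the restrictions that Procedure describes.
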